## Abstract

**Supplementary Information:**

The online version contains supplementary material available at 10.1186/s40814-024-01560-x.

## Introduction

Chronic obstructive pulmonary disease (COPD) is responsible for 873,000 ED visits and 700,000 hospitalizations each year in the United States, making it a leading cause of morbidity and mortality among Americans [1–3]. This condition, characterized by chronic symptoms such as shortness of breath, coughing, and mucus production, leads to frequent episodes of acute exacerbation [4]. Due to the frequency and severity of exacerbations, one in five COPD patients is readmitted to an inpatient facility within 30 days of hospital discharge [1–3]. Readmissions are often longer in duration and more costly than index admissions [1–3]. This leads to COPD care accounting for a disproportionate share of medical expenditure; the high level of acute care needs attributes to 70% of the $50 billion spent annually on COPD treatment [5–9]. In addition to increasing the cost of care, frequent COPD exacerbations reduce patients’ quality of life and increase their risk of COPD-related mortality [2, 10–12].

Early detection and treatment of acute COPD exacerbation have been shown to improve patient quality of life and decrease the need for emergency services utilization and hospital admission [10]. Furthermore, interventions upstream of an index admission for COPD are more effective than interventions during hospital admission or post-discharge, to prevent further admissions [9]. Put another way, the best way to prevent COPD readmission is to prevent index admission [9]. However, uncertainty remains about the optimal means of predicting and intervening upon impending COPD exacerbations.

Home monitoring systems using symptom reporting and wearable sensors show promise; small studies examining the use of daily symptom telemonitoring have shown that such surveillance facilitates the timely detection of COPD exacerbation [13–15]. However, the burden of daily symptoms and vital sign collection is onerous, and real-world evidence has demonstrated limited adherence to active vital sign collection that requires patient participation. Alternatively, passive collection of biometric data such as oxygen saturation and activity levels minimally adds to patient burden and has been shown to have prognostic value for acute care needs [16]. Further validation of the utility of biometric data signals as clinically actionable alerts for patients and their providers in real-world practice is needed. Additionally, early antibiotic and steroid therapy have been shown to improve both outcomes and patient quality of life, but to initiate treatment, clinicians must be alerted to clinical deterioration and be empowered to intervene promptly [10, 17]. Therefore, in tandem with the optimization of monitoring strategies, a systematic approach to review and respond to alerts based on consolidated data streams is needed to prevent added burden for the patients and their medical team. The present study has been designed to leverage ongoing efforts to configure a multimodal virtual care intervention for COPD patients and evaluate the feasibility of its implementation. Empowering patients with tools to help them expedite the recognition of worsening symptoms and removing barriers to care access are two critical components of improving clinical outcomes and patient quality of life.

The objective of the current study is to conduct a feasibility trial of the “Healthy at Home” program, a multimodal intervention aimed at preventing emergency services utilization and hospitalization among patients living with COPD. The program features a digital platform linked to a wearable health-monitoring device, virtual pulmonary support to facilitate complex care management, and access to an around-the-clock mobile integrated health (MIH) service that provides on-demand, in-home visits for evaluation and treatment of acute symptoms.

## Methods

### Setting and participants

This study was performed at an urban, academic tertiary care center. Inclusion criteria for participation included receiving healthcare through the hospital system of interest, being 18 years of age or older at the time of recruitment, and carrying a diagnosis of COPD. Subjects were also required to have access to a smartphone (iPhone or Android) with internet access to download and use the study apps and to live within the regional geographic area served by the system’s MIH program. Those who lacked the capacity to consent, did not understand English, did not have internet access, were enrolled in another investigational clinical trial at the time of enrollment, or were (or had previously been) enrolled in any Wellinks pulmonary support program were excluded from the study. The study was approved by the WIRB-Copernicus Group Institutional Review Board and is registered at Clinicaltrials.gov (NCT06000696).

### Recruitment

Screening for participant eligibility was performed via a query of the system’s electronic health record (EHR) for patients with a diagnosis of COPD. The number of ED visits and hospitalizations, along with the number of COPD-related medication changes in the 2 years before study enrollment, were considered proxy variables for COPD severity and treated as a count variable. We refined our recruitment to those patients that were within the second through fourth quintile of the count variable such that our cohort was comprised of patients with moderate-severity COPD. On a per-case basis, exceptions to this strategy were accommodated when patients were directly referred to the research team by the clinical team.

All participants were initially invited via email. Non-response to email solicitation was followed by two text messages within 2 weeks of the email invitation and a paper mailer sent to prospective participants’ homes. Patients who were identified as prospective participants and who were hospitalized or had upcoming ambulatory pulmonary clinic appointments were approached in person by the study team at the medical center. Finally, flyers advertising the study were placed in high-visibility places such as clinic waiting rooms. The recruitment strategy and number of participants approached are summarized in Fig. 1. Invitations for recruitment were conducted in waves ranging from 500 to 3000 patients based on the composition of the study cohort after each cycle to achieve a balanced representation of risk categories and sociodemographic factors.

**Fig. 1 Fig1:**
[figure not shown]
Participant recruitment workflow: Potential participants were primarily identified via a query of the institutional electronic health record and invited via email, followed by paper mailers and SMS messages. Potential participants who were hospitalized or attending ambulatory appointments were approached by the study team in person or self-identified themselves from flyers advertising the study

### Procedure

Participants who expressed interest in participating were given instructions to download the study app, a custom interface created through the MyDataHelps platform (Supplemental File 1). MyDataHelps is a mobile application created by CareEvolution to give a platform for researchers and participants to engage in clinical research. Through this study app, participants completed eligibility questions to ensure that they met all inclusion criteria for the study. If they were determined to be eligible, participants were subsequently prompted to digitally review and sign an informed consent form through the study app. Because eligibility screening and enrollment could be performed through the app, participants could enroll entirely remotely.

Once participants completed consenting procedures, a welcome kit was shipped to their residence containing all necessary study-related materials including a Fitbit Charge 5 smartwatch and additional literature about the study and the affiliate MIH program. Subjects were then prompted to schedule an onboarding call with a member of the study team where they were guided through setting up and using the smartwatch, educated on the use of the study app, and provided any additional support needed to initiate participation in the study. Once onboarded, participants were asked to partake in study procedures for 6 months. A summary of all components of the study and their interconnectedness is depicted in Table 1. A Standard Protocol Items: Recommendations for Intervention Trials (SPIRIT) Figure for the study is depicted in Fig. 2.

**Fig. 2 Fig2:**
[figure not shown]
SPIRIT depictionof study activity and outcomes

**Table 1 Tab1:** Healthy at home intervention components: This multimodal intervention included a study app, smartwatch, access to acute care through a mobile integrated health program and virtual pulmonary support services

Intervention component	Description	Interaction with other components	All participants or opt-in
MyDataHelps App (main study app)	Houses all participant-facing forms and questionnaires including screening and consent. Prompts participants to complete scheduled assessments. Receives information from biosensors and is linked to participants’ EHR and claims data to aggregate all data streams. Generates momentary assessments triggered by participant responses or biometric data	All participant-level MyDataHelps data is visible to the Wellinks and MIH team on the study dashboard. Clinical data can trigger alert to participants through the app suggesting a home assessment from the MIH team and connect participants directly with the MIH visit request line	All
Fitbit Smartwatch	Collects biometric data. All data is visible to participants, study team, MIH clinicians, and Wellinks coaches through the MyDataHelps	Biometric patterns trigger alert to patients suggesting MIH visits. Biometric data is visible to clinical and research teams	All
Mobile Integrated Health Program (community paramedics and MIH physicians)	Community paramedics are available on-demand to perform home visits to evaluate and treat participants experiencing acute symptoms with support from a supervising physician. The program is specifically equipped to initiate treatment for COPD exacerbation	MIH team can view participant-level data in MyDataHelps. MIH visits offered to participants reporting worsening symptoms or exhibiting concerning biometric data through the study app. Research and Wellinks team refer participants to MIH team for all acute clinical concerns	All
Wellinks Virtual Pulmonary Rehabilitation Program	Coaching program to support participant education, treatment adherence, and goal setting, as well as a virtual pulmonary rehabilitation. Hosted on a separate program-specific app	Wellinks team can view participant-level data in MyDataHelps to support coaching plans. Wellinks can contact MIH team with any acute concerns requiring clinical evaluation	Opt-In
Wellinks equipment kit (spirometer, pulse oximeter, exercise equipment	Used with the Wellinks team to support pulmonary coaching plan and collect additional relevant biometric data	Spirometry and pulse oximetry data is integrated with the MyDataHelps app and is visible to the study and clinical teams	Opt-In

### Participant reported outcomes

Study participants were asked to complete a series of instruments throughout the 6-month study period through the MyDataHelps app. Participants were notified of outstanding surveys and prompted to complete them through app push notifications according to the study schedule. In addition to demographic questions asked at baseline, participants were prompted to complete surveys including the NIH-PROMIS COPD questionnaires, Patient Activation Measure, Modified Medical Research Council Dyspnea Scale, and a patient satisfaction measure at enrollment, 3 months, and 6 months (Table 2) [18–21]. Participants were also prompted to complete the COPD Assessment Test monthly and a single-item wellness measure weekly [22]. Momentary assessments for participants were assessed using CLEAR-Sx, Ex, and Rx tools; these were triggered based on participants reporting not feeling well on the single-item wellness measure or by wearable device data (Table 3) [16, 23].

**Table 2 Tab2:** Participant-facing assessments: Participants were prompted to complete all assessments through the Care Evolution Healthy At Home study app. The app prompted participants to complete each assessment as they were due and sent reminders for delinquent assessments

Questionnaire	Frequency
Baseline	Once (available upon enrollment)
COPD Assessment Test	Monthly
NIH-PROMIS COPD	0, 3, and 6 months
CLEAR-Sx, Ex, and Rx	Ad hoc (administered when metrics such as oxygen saturation, spirometry data [if available], activity indices [if available] indicate a potential COPD exacerbation)
Patient Activation Measure	0, 3, and 6 months
mmRC (Modified Medical Research Council) Dyspnea Scale	0, 3, and 6 months
Patient Satisfaction	0, 3, and 6 months
Single-item wellness	Weekly
Exit Survey	6 months

**Table 3 Tab3:** Clinical alert triggers. The clinical alert metrics triggered app notifications to prompt participants to request a medical evaluation if they were feeling unwell. The app enabled participants to quickly call the mobile integrated team for an on-demand acute home visit with a “one-touch” option to dial the MIH hotline phone number

Metric	Definition for flag in dashboard
SpO2 (triggers CLEAR-Sx, Ex, Rx survey)	Fall in SpO2 below 90% for 2 consecutive days or a fall of 4% or higher below 7-day rolling average for 2 consecutive days
FEV1, FVC, PEF, and IC (triggers CLEAR-Sx, Ex, Rx survey)	Fall of 1.65 SD or greater below 7-day rolling average for 2 consecutive days
Quality of Activity (triggers CLEAR-Sx, Ex, Rx survey)	Calculated from Activity Index and Regularity Index. Fall of 1.65 SD or greater below 7-day rolling average for 2 consecutive days
Exacerbation (categorized by answers to CLEAR Sx, Ex, and Rx survey)	Anthonisen criteria (Category I, II, or III) based on self-report of symptom data

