### Virtual comprehensive pulmonary support service

All participants were presented with the option to enroll in a virtual pulmonary care program that provides multimodal support for COPD patients, through a company called Wellinks. The option to enroll in this was made available through the MyDataHelps during the first 90 days of study participation. The program includes coaching to support participant education, treatment adherence, and goal setting, and a virtual pulmonary rehabilitation program that provides a home-based exercise plan including safety instructions and COPD-specific breathing techniques. Additionally, Wellinks participants received a second equipment kit containing a spirometer, pulse oximeter, ten-foot tape measure, exercise band, and an exercise guide. The virtual pulmonary support program team coordinated introductory calls with participants to download their app and configure the spirometer and pulse oximeter devices via Bluetooth which are used to collect additional biometric data. After a comprehensive personalized assessment, a schedule for regular sessions with a health coach was created for participants. All coaching was scheduled and joined through the program’s app, with board-certified health and wellness coaches or nurse practitioners.

In the event of an acute clinical concern, the Wellinks team’s protocol was to instruct participants to contact the MIH clinician or their healthcare provider. The Wellinks team was also empowered to contact the on-duty MIH clinician directly. Participants who enrolled in the Wellinks program were classified as the “full-intervention” group, and those who enrolled in the study but opted not to participate in the Wellinks program were considered the “partial-intervention” group.

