### All feasibility outcomes will be reported descriptively

Clinical and operational efficacy will be compared across all three groups of COPD participants: full-intervention, partial-intervention, and a control group (no intervention) identified from the EMR using a novel synthetic control study strategy that has been endorsed by the FDA for generating real-world evidence [26, 27]. The clinical efficacy measures include medication requirements, healthcare utilization related to acute or urgent care, total medical expenditure, and, in the intervention arms, participant-reported outcomes (COPD severity, COPD exacerbations, patient activation measure, patient satisfaction, modified Medical Research Council Dyspnea Scale). Lastly, operational efficacy includes time spent during MIH visits, MIH visit escalation to acute care rate, and care management time.

Descriptive analysis will be used to characterize the feasibility outcomes. Continuous measures will be described using mean or median depending on the underlying distribution, and categorical variables will be described as proportions. Associations with sociodemographic characteristics and GOLD classification of COPD severity will be assessed for feasibility outcomes. Count models (Poisson, negative binomial, or zero-inflated negative binomial) will be used to compare healthcare utilization over the course of the study. Continuous models will be used to compare medical expenditure. GEE models with logit or linear link will be used to assess changes over time for COPD severity measurements. Table 5 depicts planned clinical and operational outcomes, operationalization of measurements, and preliminary analysis plans for each outcome.

**Table 5 Tab5:** Clinical and operational outcomes: A summary of chosen clinical outcomes, operationalization of measurement, analysis plan

Conceptual outcome	Operational measure	Analysis plan
Participant perceived COPD severity	• Patient Activation Measure • (Modified Medical Research Council) Dyspnea Scale	All instrument scores will be treated as continuous variables. Regression will be performed using GEE models with logit or linear link. Scores will be compared from participants at baseline and 3 and 6 months
Patient quality of life	• COPD Assessment Test • NIH-PROMIS COPD • Single Item Wellness	
Patient satisfaction	• Patient Satisfaction Measure • Study Exit Survey	

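### One CLEAR survey trigger, spirometry, exists only in the full-intervention group, so a full-versus-partial comparison of CLEAR-based exacerbations is open to detection bias

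*Protocol article*

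**What the plan says.** **How the survey is opened.** Under Participant reported outcomes, the text says of the CLEAR assessments that "these were triggered based on participants reporting not feeling well on the single-item wellness measure or by wearable device data". Table 2 lists CLEAR as ad hoc and names spirometry, where available, among the metrics that prompt it. Table 3 gives the flags: SpO2, Quality of Activity, and "FEV1, FVC, PEF, and IC (triggers CLEAR-Sx, Ex, Rx survey"), the last defined as "Fall of 1.65 SD or greater below 7-day rolling average for 2 consecutive days".

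**How an exacerbation is classified.** The last row of Table 3 reads "Exacerbation (categorized by answers to CLEAR Sx, Ex, and Rx survey") and applies the Anthonisen categories to self-reported symptoms.

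**Who has which device.** Table 1 gives the smartwatch to everyone. The section on the virtual pulmonary support service says "Wellinks participants received a second equipment kit containing a spirometer, pulse oximeter", and Table 1 adds that "Spirometry and pulse oximetry data is integrated with the MyDataHelps app". The same section makes Wellinks participants the full-intervention group, while "those who enrolled in the study but opted not to participate in the Wellinks program were considered the" partial-intervention group.

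**What is compared.** The Analysis plan says that clinical efficacy will be compared across the full, partial and control groups. In the intervention arms it includes "participant-reported outcomes (COPD severity, COPD exacerbations, patient activation measure, patient satisfaction, modified Medical Research Council Dyspnea Scale"). The article states no restriction to triggers that both groups share.

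**The concern.** CLEAR is not a scheduled instrument. An episode enters a CLEAR-based count only if something opens the survey and the participant then reports qualifying symptoms. If one group has more ways of opening it, that group can record more episodes at the same underlying rate.

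Here the extra route is not incidental. The spirometer comes with Wellinks, and Wellinks enrolment defines the group, so the means of detection differs by group by design.

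The likely direction is against the full-intervention group. A real reduction in exacerbations could be diluted or hidden, and no difference could appear as a small excess. The study is a feasibility pilot, but the Discussion presents it as preparation for a larger study of clinical outcomes, so the same measurement rule could carry forward.

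**Working it through.** **1. Trigger routes by group**

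| Route to a CLEAR survey | Full | Partial | Source |
|---|---|---|---|
| Weekly single-item wellness measure | yes | yes | Participant reported outcomes, Table 2 |
| Smartwatch SpO2 | yes | yes | Tables 1 and 3; Remote patient activity monitoring |
| Quality of Activity | yes | yes | Table 3 |
| FEV1, FVC, PEF, IC | yes | no | Tables 1 and 3; Wellinks section |
| Kit pulse oximeter SpO2 | possibly | no | Table 1; Table 3 does not say which device supplies SpO2 |

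Three routes are common. One, spirometry, is confined to the full group, with a possible second source of SpO2.

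**2. Effect on an apparent rate ratio**

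The article states no exacerbation rate, frequency of spirometry, survey response rate or group sizes, so there is no figure of its own to reproduce. The following is an illustration on assumed values.

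Let *ps* be the probability that the shared triggers catch a true episode, and *px* the probability that spirometry catches it. Take the two as independent. The partial group records a fraction *ps* of episodes and the full group records 1 − (1 − *ps*)(1 − *px*). With a true ratio of 1:

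apparent ratio = [1 − (1 − *ps*)(1 − *px*)] / *ps*

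| *ps* | *px* = 0.1 | *px* = 0.5 |
|---|---|---|
| 0.9 | (1 − 0.1 × 0.9)/0.9 = 1.01 | (1 − 0.1 × 0.5)/0.9 = 1.06 |
| 0.7 | (1 − 0.3 × 0.9)/0.7 = 1.04 | (1 − 0.3 × 0.5)/0.7 = 1.21 |
| 0.5 | (1 − 0.5 × 0.9)/0.5 = 1.10 | (1 − 0.5 × 0.5)/0.5 = 1.50 |

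In the middle row at *px* = 0.5, a true ratio of 1/1.21 = 0.83 would appear as no difference. If spirometry tends to catch the same episodes as the shared triggers, the distortion is smaller than shown.

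**3. How often spirometry could open a survey by chance**

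A single normal reading falls 1.65 SD below a known mean with probability 0.0495; two independent days give 0.0495² = 0.0024. The rule was simulated for 4,000 stable participants over 180 days. The assumptions were daily spirometry, independent normal readings from day to day, the previous 7 days as reference, and correlation of 0.3 to 0.9 among the four metrics. It gave 1.3 to 2.2 flag episodes per participant with the SD known, and 2.6 to 3.9 with the SD estimated from the 7-day window. These are extra prompts, not extra exacerbations.

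**4. After the change**

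If only episodes for which a shared trigger fired are counted, *px* drops out: apparent ratio = *ps*/*ps* = 1.00 when the true ratio is 1.

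**The case against.** Five points can be made against this.

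- **Most triggers are shared.** This stands. A reader might infer that only the full group's extra devices open the survey. The document does not support that: the wellness item, smartwatch SpO2 and activity routes are open to everyone. The text sentence on triggers even omits spirometry, although Tables 2 and 3 both include it.
- **A prompt is not an exacerbation.** This stands. The chance flags in step 3 should not be read as false exacerbations, because the participant must still report symptoms that meet the Anthonisen criteria. The bias arises through true episodes that the shared triggers would miss.
- **Daily spirometry is assumed.** This stands. Table 1 ties the kit to the coaching plan and gives no frequency. The flag needs two consecutive days, so intermittent use could make it rare.
- **Table 5 has no exacerbation row.** This limits the scope. Its between-group count outcomes are medication changes, ED visits and COPD-related hospitalizations, none defined by CLEAR. A reader might extend the bias to them, but this mechanism does not reach how they are counted.
- **The outcome definition may sit in a fuller document.** This stands only in part. The article does not say outright that the efficacy outcome is the Table 3 flag. But the only classification of exacerbations it gives is from CLEAR answers, and it lists exacerbations as a participant-reported efficacy measure. The unequal triggers are stated in the article itself; they are not an omitted detail.

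**Conclusion.** The concern holds for CLEAR-based exacerbations in the full-versus-partial comparison and no further. One trigger, plus possibly a second SpO2 source, is available only to the full group, and the plan as written gives the two groups unequal opportunity for detection.

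The expected direction is more recorded events in the full group. The size is unknown: anything from negligible, where shared triggers catch 90% of episodes, to 1.50, where they catch 50% and spirometry catches 50%. All of these probabilities, and their independence, are assumptions.

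It would go too far to say that Wellinks will look harmful. Nothing in the document fixes how often spirometry is done or how many episodes it alone would find. In a feasibility pilot this is a modest flaw, worth correcting because correction is cheap.

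**What to change.** 1. Record the source of every CLEAR survey, keeping all triggers that fired during an episode and not only the first. If only the first were kept, full-group episodes that spirometry happened to flag ahead of a shared trigger would be dropped, and the bias would reverse.
2. In the full-versus-partial comparison, count only episodes for which a trigger common to both groups fired: wellness item, smartwatch SpO2 or activity. Keep smartwatch and kit-oximeter SpO2 separate.
3. Report episodes found only by the spirometer or kit oximeter descriptively, for the full group.
4. Rest any three-group comparison on the outcomes already in Table 5 that do not depend on CLEAR: ED visits, COPD-related hospitalizations and COPD-related medication changes.

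The cost is a source field in the app data and a few lines in the analysis plan. Some full-group episodes leave the comparison, with some loss of information. Alerts and care are unchanged.
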